#### Sample size calculation

Literature search failed to identify a study of similar design to this one. In an observational study by Wizemann et al.
[1] of 269 MHD patients the patients were divided into hypervolemic group if their ECF was 15% higher than normal or normohydrated group if less than 15%. The patients were followed for an average 3.5 years. There was 41% death in the hypervolemic group, and 30% death in normohydrated group. Relative risk of death was 36.6% higher in hypervolemic group than in the other.

According to data from Beijing Hemodialysis Quality Control and Improvement Center, the annual mortality rate of Beijing MHD patients is around 10%, it is estimated that 3 year mortality to be 30%. It is also estimated that the rate of composite endpoint within 3 year period of time is 40%. We make an assumption that BCM guided fluid management will reduce the 3-year composite endpoint rate from 40% to 32% (20% relative risk reduction). To reach statistical significance with α < 0.05 and 1-β > 80%, the sample size required is 1128. Allowing for a 20% loss-to-follow-up, the total sample size planned is 1354.

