**Methods:**

This is a multicenter, prospective, randomized, controlled trial. More than 1300 participants from 16 clinical sites will be included in the study. The enrolment period will last 6 months, and minimum length of follow-up will be 36 months. MHD patients aged between 18 years and 80 years who have been on MHD for at least 3 months and meet eligibility criteria will be invited to participate in the study. Participants will be randomized to BIA arm or control arm in a 1:1 ratio. A portable whole body bioimpedance spectroscopy device (BCM—Fresenius Medical Care D GmbH) will be used for BIA measurement at baseline for both arms of the study. In the BIA arm, additional BCM measurements will be performed every 2 months. The primary intent-to-treat analysis will compare outcomes for a composite endpoint of death, acute myocardial infarction, stroke or incident peripheral arterial occlusive disease between groups. Secondary endpoints will include left ventricular wall thickness, blood pressure, medications, and incidence and length of hospitalization.

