## Methods

### Study design

This is an open label, multicenter, prospective, randomized controlled trial. The aim of the study is to assess if BIS guided fluid management can improve long term outcome in MHD patients. Body composition and hydration state will be assessed with a portable whole body bioimpedance spectroscopy device (BCM—Fresenius Medical Care D GmbH). The study will involve 16 clinical sites, enrolling more than 1300 participants. The enrolment period will last approximately 6 months, with a planned minimum 36 months follow-up period. Participants will be randomized to two arms, the control arm and BCM arm. Patients in both arms will receive BCM measurement, but results from the BCM measurement in the control group will be kept blinded to the investigators. Participants in control group will be followed up and their dry weights will be adjusted according to the dialysis center’s standard clinical practice. Clinicians managing participants in the BCM group, in addition to routine practice, will receive BCM measurement and dry weight will be adjusted according to BCM output data estimating overhydration and dry weight. All of baseline demographics, clinical data, laboratory data, regular BCM measurement, and ultrasonic cardiograph (UCG) data will be recorded on study case report forms (CRFs).

The flow chart of the study is shown in Figure
1.

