#### Analytical method

##### Primary endpoint

The primary analysis will be an intent-to-treat analysis comparing composite endpoint between the BCM and the control arms. The intent-to-treat population is defined as all enrolled study participants. For this analysis, the follow-up time begins from the enrollment date to the composite endpoint, loss to follow-up, or end of study.

Multivariate Cox proportional hazards regression models will be used for analysis of the risk of death comparing BCM and control arms, with adjustment for age, sex, dialysis vintage, primary cause of ESRD, comorbid conditions, and other characteristics that may be associated with increased risk of death, such as inter-dialysis weight gain, hypertension and hsCRP.

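### The planned 1354 is 1128 multiplied by 1.2; allowing for 20% loss means dividing by 0.8, which gives 1410

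*Protocol article*

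**What the plan says.** All of the calculation stands in the protocol article under Sample size calculation. The effect assumed is to "reduce the 3-year composite endpoint rate from 40% to 32% (20% relative risk reduction". The requirement follows: "To reach statistical significance with α < 0.05 and 1-β > 80%, the sample size required is 1128". The allowance for loss comes next: "Allowing for a 20% loss-to-follow-up, the total sample size planned is 1354". The abstract gives equal allocation: "Participants will be randomized to BIA arm or control arm in a 1:1 ratio".

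Two other statements bear on the point. Under Primary endpoint, in the analytical methods, "the follow-up time begins from the enrollment date to the composite endpoint, loss to follow-up, or end of study". Under Study design, patients are to be followed "with a planned minimum 36 months follow-up period".

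The sample size paragraph also reports that "the annual mortality rate of Beijing MHD patients is around 10%, it is estimated that 3 year mortality to be 30" percent. The composite rate is then introduced as an estimate of its own: "It is also estimated that the rate of composite endpoint within 3 year period of time is 40" percent.

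**The concern.** An allowance for loss should leave the required number in the analysis after the loss has occurred. Raising the requirement by 20% does not do this, because the 20% loss then applies to the larger, enrolled number. The paragraph claims power above 80% and a 20% loss allowance together, and on its own method 1354 does not deliver both. There is no slack to absorb the slip, since 1128 gives 80.0% and no more. At stake is whether the stated size, loss and power agree with one another. It matters a little more here because the Interim analysis section plans to adjust the sample size from accruing data, and that adjustment needs a sound starting calculation.

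**Working it through.** **Inputs.** From Sample size calculation: control rate 0.40, BCM rate 0.32, α = 0.05, power 80%, loss 20%, planned total 1354. From the abstract: 1:1 allocation. The article does not say whether α is one- or two-sided. Two-sided reproduces the stated figure; one-sided gives 890 and does not.

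**1. Reproduce 1128.** Pooled two-proportion formula without continuity correction, mean rate 0.36:

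n per arm = [1.960 × √(2 × 0.36 × 0.64) + 0.842 × √(0.40 × 0.60 + 0.32 × 0.68)]² / 0.08²

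= [1.960 × 0.6788 + 0.842 × 0.6765]² / 0.0064 = [1.3305 + 0.5693]² / 0.0064 = 563.9

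Rounded up, this is 564 per arm, or 1128 in total: an exact match.

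**2. Reproduce 1354.** 1128 × (1 + 0.20) = 1353.6, rounded up to 1354. This is the operation that was used.

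**3. Correct allowance.** 1128 / (1 − 0.20) = 1410, which is 56 more than 1354 (56 / 1354 = 4.1%).

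**4. What 1354 covers.**
- After 20% loss: 1354 × 0.80 = 1083.2, so 1083 evaluable, and 1128 − 1083 = 45 short.
- Largest loss that still leaves 1128: 1 − 1128 / 1354 = 16.7%.

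**5. Power at 1083 by the formula of step 1.** With 541.6 per arm:

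z = (0.08 × √541.6 − 1.3305) / 0.6765 = 0.785, so power = 78.4%.

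This is 1.6 points below 80%.

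**6. Power if lost patients count until loss.** This follows the definition of follow-up time under Primary endpoint. Assumptions that the article does not state: constant hazards in each arm, and exponential loss reaching 20% at 3 years.
- Hazard ratio implied by 40% and 32%: ln 0.68 / ln 0.60 = 0.755.
- Annual hazards: control −ln 0.60 / 3 = 0.1703; BCM −ln 0.68 / 3 = 0.1286; loss −ln 0.80 / 3 = 0.0744.
- Probability of an observed event by time T: h / (h + 0.0744) × [1 − exp(−(h + 0.0744)T)], where h is the arm's event hazard.
- T = 3 years: 0.362 and 0.289, so 677 × (0.362 + 0.289) ≈ 441 events. Schoenfeld power = Φ(½ × √441 × 0.281 − 1.960) = about 84%.
- T = 3.25 years on average (6 months of enrolment, then at least 36 months): about 465 events and about 86%.

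**7. Mortality figure, as a side check.** 10% a year compounds to 1 − 0.9³ = 27.1% over 3 years; 30% is 3 × 10%. The formula in step 1 uses only 0.40 and 0.32, so this figure changes neither 1128 nor 1354.

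**The case against.** The strongest objection is that the slip has almost no consequence. The shortfall is 1.6 points, and it appears only if every lost patient contributes nothing. The primary analysis takes all enrolled participants and counts their time up to loss, so partial follow-up is used and power is likely to stay above 80%. This stands, and it limits the point to how the paragraph is written. It does not rescue the paragraph, which argues from two proportions and a loss allowance and never appeals to partial follow-up.

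Two stronger readings are tempting. The first is that the trial is underpowered. The documents do not support this, because the 78.4% belongs to the worst case and the planned handling of follow-up points to 84% to 86% under the loss pattern assumed above.

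The second is that multiplying 10% by 3 inflates the composite rate and so also costs power. The documents do not support this either. The 30% is not an input to 1128, and the 40% is given as a separate estimate with no formula linking the two. Any lower composite rate would be the reader's own assumption. The source rate is also only approximate: 30% at 3 years corresponds to 11.2% a year, not far from a rate given as about 10%.

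**Conclusion.** The paragraph is wrong as written. For the stated 20% loss the total is 1410, not 1354, and by the formula that yields 1128 the planned number gives 78.4% power with 1083 evaluable patients. This part rests only on the plan's inputs and a two-sided test, and is certain. The practical effect is small: 1.6 points at worst, and probably no shortfall once follow-up to the time of loss is counted. The 84% to 86% range depends on assumed constant hazards and exponential loss, so it indicates likely power and does not replace the plan's own calculation. The 30% mortality figure is a minor imprecision with no bearing on the sample size.

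**What to change.** Reword the paragraph and leave enrolment as planned. Either of two statements would be correct:
- 1354 allows for a loss of 16.7% at 80% power; or
- a loss of 20% would need 1410, and 1354 then gives 78.4% by the two-proportion formula if lost patients contribute nothing.

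Optionally, add the power of 1354 on a time-to-event basis, with the assumed loss pattern stated beside it. In passing, the 3-year mortality could be given as about 27% if the annual rate is taken as 10%.

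The cost is one edited paragraph and a slightly less favourable stated figure. No further patients are needed.

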#### Analytical method

##### Primary endpoint

The primary analysis will be an intent-to-treat analysis comparing composite endpoint between the BCM and the control arms. The intent-to-treat population is defined as all enrolled study participants. For this analysis, the follow-up time begins from the enrollment date to the composite endpoint, loss to follow-up, or end of study.

Multivariate Cox proportional hazards regression models will be used for analysis of the risk of death comparing BCM and control arms, with adjustment for age, sex, dialysis vintage, primary cause of ESRD, comorbid conditions, and other characteristics that may be associated with increased risk of death, such as inter-dialysis weight gain, hypertension and hsCRP.

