#### Primary objective

The primary objective of the study is to compare incidence rate of a composite endpoint between BCM group and control group. Participants reach the primary endpoint if at least one of the following occurs: (1) death, (2) acute myocardial infarction, (3) cerebral thrombosis, (4) cerebral hemorrhage, (5) peripheral arterial occlusive disease. The diagnosis of endpoints will be made by the Endpoint Committee.

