### Endpoint and sample size

Annual mortality of Beijing MHD patients was around 10%. To reach statistical significance, the sample size will be very large. By using composite endpoint, the sample size becomes reasonable and feasible.

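### The only model given under Primary endpoint is for death, although the same section and the rest of the plan make the composite the primary comparison

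*Protocol article*

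**What the plan says.** All references are to the Protocol article.

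- **Primary objective:** "The primary objective of the study is to compare incidence rate of a composite endpoint between BCM group and control group". The components are death, acute myocardial infarction, cerebral thrombosis, cerebral haemorrhage and peripheral arterial occlusive disease. Study hypotheses tests the same kind of composite.
- **Sample size calculation:** the trial is sized on the assumption that the intervention will "reduce the 3-year composite endpoint rate from 40% to 32% (20% relative risk reduction"), which gives 1128 patients, or 1354 after an allowance for loss. The same section puts 3-year mortality at 30%.
- **Analytical method, Primary endpoint, first paragraph:** "The primary analysis will be an intent-to-treat analysis comparing composite endpoint between the BCM and the control arms". For this analysis, "the follow-up time begins from the enrollment date to the composite endpoint, loss to follow-up, or end of study".
- **Same heading, second paragraph:** "Multivariate Cox proportional hazards regression models will be used for analysis of the risk of death comparing BCM and control arms". The adjustment set ends with "other characteristics that may be associated with increased risk of death", followed by three examples.
- **Secondary objectives and Secondary endpoint:** these cover left ventricular measures, blood pressure, antihypertensive medication and hospitalisation. Death alone is in neither list.
- **Discussions, Endpoint and sample size**, on why mortality was not chosen: "To reach statistical significance, the sample size will be very large. By using composite endpoint, the sample size becomes reasonable and feasible".

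**The concern.** The section sets up a time-to-event comparison of the composite, then attaches its only named model, a multivariable Cox regression, to death. The mention of death in the covariate rationale as well makes a single slip of the pen less likely. The death model cannot be read as a declared secondary analysis, because no secondary list contains death.

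If the sentence is followed literally, the hazard ratio reported under the primary endpoint ignores non-fatal myocardial infarction, stroke and peripheral arterial disease. These events are the reason for having a composite. The estimate would also be for an effect on which the plan makes no assumption and for which it was not sized. If the sentence is only loose wording for the composite, it still misstates the analysis and needs correcting.

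**Working it through.** **1. Inputs.** From Sample size calculation: composite 40% against 32% at 3 years, 3-year mortality 30%, α 0.05, power 80%, N = 1128. From the Abstract: 1:1 allocation. The plan does not say whether the test is two-sided, but a two-sided test reproduces its N. The effect on death is *not in the plan*, so a range of relative reductions from 10% to 25% is assumed.

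**2. The plan's own figure.** Two-sided comparison of two proportions, pooled variance, no continuity correction:

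n per arm = [1.960·√(2p̄(1−p̄)) + 0.842·√(p₁q₁ + p₂q₂)]² / (p₁ − p₂)²

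With 0.40 and 0.32, p̄ = 0.36 and n = (1.330 + 0.569)² / 0.08² = 564. The total is 1128, exactly as stated, so the sizing is for the composite.

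**3. Does that size support a Cox model on the composite?** Under constant hazards, HR = ln(0.68)/ln(0.60) = 0.755. Events needed (Schoenfeld) = 4(1.960 + 0.842)²/(ln 0.755)² = 398. Events expected = 1128 × 0.36 = 406. Power is about 81%, so it does.

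**4. The same N for death alone**, from 30% control mortality, two-proportion formula:

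| Assumed reduction in death | Rates | Power at N = 1128 | N for 80% power, before loss |
|---|---|---|---|
| 10% | 30% vs 27% | 20% | 7108 |
| 15% | 30% vs 25.5% | 39% | 3108 |
| 20% | 30% vs 24% | 62% | 1718 |
| 25% | 30% vs 22.5% | 82% | 1080 |

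Cox check on the 20% row: HR = ln(0.76)/ln(0.70) = 0.769. About 458 events are needed against 1128 × 0.27 = 305 expected, for power of about 63%.

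**5. Sensitivity.**
- If all 1354 were fully followed, a 20% reduction in death would have about 70% power.
- If 10% a year is compounded, 3-year mortality is 1 − 0.9³ = 27.1%. Power at 1128 for a 20% reduction is then 56%.
- If the composite's hazard ratio of 0.755 applied to death from 30%, power at 1128 would be about 69%.

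**6. What the death model leaves out.** On the plan's control rates, 40% − 30% = 10 points. So about a quarter (10/40) of control patients with a composite event within 3 years would not be events in the death model.

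**The case against.** The strongest reply is that the primary analysis is not in doubt. The section's first sentence names the composite, the follow-up clock stops at the composite, and the objective, hypothesis, sizing, Limitations and Conclusion all agree. The death model is in a separate paragraph and is never called primary. This stands, and it limits the point. A reader might infer that the pre-specified primary test has been switched to death, or that the plan offers two equal primary results to choose from. The text does not support either reading. A report that presented death as the primary result would contradict most of the document.

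It can also be said that a condensed article may leave the composite's test to the full protocol or analysis plan. That is right, and the unnamed test would not be a finding by itself. What remains is an analysis that the article does state, under the primary heading, with the wrong outcome and with covariates chosen for that outcome.

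Finally, a reader might infer that the trial is simply underpowered because of this sentence. The plan gives no effect on death, so that is conditional: at a 25% reduction, power passes 80%. The only mortality contrast in the plan, 41% against 30% (11/41, about 27% relative), is observational and is not a treatment effect. The plan's own statement that a mortality endpoint would need a very large sample supports the direction of the concern, but not a particular power figure.

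**Conclusion.** The point holds as an internal contradiction. The Primary endpoint section declares a comparison of the composite and then gives, as its only model, a Cox regression for death. That conflicts with its own first paragraph and with Primary objective, Study hypotheses and Sample size calculation.

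The mismatch does not depend on any assumed effect; its cost in power does. At N = 1128 with 30% control mortality, power for death runs from about 20% to 82% as the assumed reduction goes from 10% to 25%. For the composite it is 80% by the plan's own calculation. These figures assume 1128 patients with complete 3-year outcome, a two-sided 5% test and, for the Cox checks, constant hazards. Whether the allowance for loss leaves 1128 such patients is a separate question and is not part of this point.

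This should be fixed. It falls short of a fatal flaw, because every other element of the design identifies the composite as primary.

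**What to change.** Reword the second paragraph of Primary endpoint in three respects:

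1. State that the Cox model is fitted to time from the enrolment date, the origin that the section already uses, to the first composite event, and that its treatment hazard ratio is the single primary result.
2. Close the covariate list before any comparison by arm. Use named variables at their baseline values, chosen for association with the composite. As written the list is open-ended, and hsCRP and blood pressure are also measured during follow-up. Moving the model to the composite without closing the list would carry that discretion into the primary test.
3. Label any death-only model as secondary or supportive, and add death to the secondary list if it is kept.

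The cost is a few sentences in the protocol or analysis plan. No extra data, patients or visits are needed, and the planned size already supports a Cox analysis of the composite (about 81% power at 1128).

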##### Baseline data collection

In brief, baseline data are collected before initiation of BCM monitoring and include demographics, ESRD treatment history, current vascular access type, detailed comorbid conditions assessment, current dialysis prescription and medications (oral, subcutaneous and intravenous), CBC, routine laboratory data, Kt/V, iPTH and hsCRP. UCG will also be performed. BCM measurement will be done in participants in both BCM arm and control arm. In the control arm, BCM data will not be provided to patient care provider. 24 hours urine volume will be recorded the day before dialysis session. A physical examination will be performed.

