#### Dry Weight Adjustment Strategy

All participants will be educated to reduce inter-dialysis weight gain to less than 5% body weight.

For participants in the control arm, dry weight will be adjusted according to the clinical site’s standard clinical practice.

For participants in the BCM arm, dry weight will be adjusted according to the BCM estimates of overhydration and normovolemic weight. During each dialysis session, participants’ dry weight will be increased or decreased toward BCM reported dry weight. The increment or decrement of dry weight will not be greater than 0.5 Kg within a single dialysis session. Thus, in this arm participants’ dry weights will be gradually adjusted to BCM reported value. If ultrafiltration is not tolerated because of hypovolemia based on symptoms and signs, such as muscle cramps, need for excessive saline, or symptomatic hypotension, adverse events will be recorded, and the actual dry weight will be adjusted by plus 0.5 Kg. If participants experience hypervolemic clinical episodes, such as hypertension related symptom, congestive heart failure, pulmonary edema, adverse events will also be recorded. If a patient experiences the same adverse effect of dry weight change for two consecutive visits, the patient will be removed from the study because of adverse event.

Dry weight adjustment flow chart in the BCM arm is shown in Figure
2.

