### Changes of dialysis prescription and medications

Fluid status change will definitely lead to physiological changes of the body. It is reasonable that some clinical parameter will change, like blood pressure, hemoglobin, hsCRP, BNP. So it is reasonable to allow dialysis prescription and medications change, which will serve as one of the secondary endpoints.

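### The Cox model's open covariate list names hypertension and hsCRP without limiting them to baseline, although the protocol expects both to respond to fluid management

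*Protocol article*

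**What the plan says.** All references are to the protocol article.

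- **The model.** Under Analytical method, Primary endpoint, the primary analysis is an intent-to-treat comparison of the composite between arms, and that sentence names no covariates. The next paragraph gives a multivariable Cox model for the risk of death. It adjusts for age, sex, dialysis vintage, cause of ESRD, comorbid conditions and "other characteristics that may be associated with increased risk of death, such as inter-dialysis weight gain, hypertension and hsCRP". No measurement time is given for any of these.
- **Expected response to treatment.** The discussion of prescription and medication changes says of shifts in fluid status: "It is reasonable that some clinical parameter will change, like blood pressure, hemoglobin, hsCRP, BNP". Study hypotheses makes better blood pressure control a secondary hypothesis, and blood pressure is a secondary endpoint.
- **Repeat measurement.** Table 1 schedules blood pressure (within the physical examination) every 2 months and hsCRP every 3 months after baseline.
- **Baseline overhydration.** Baseline data collection states: "BCM measurement will be done in participants in both BCM arm and control arm". Overhydration is not named among the covariates.
- **Site.** In the control arm, "dry weight will be adjusted according to the clinical site"'s usual practice. Site is not named in the model either.

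**The concern.** A covariate that treatment can change is safe in a randomised comparison only if its value was fixed before randomisation. Adjusting for a later value estimates the part of the effect that does not pass through that variable, which is not the effect the trial sets out to measure. Two of the three examples in the list, hypertension and hsCRP, concern quantities that the protocol itself expects fluid management to move, and both exist as baseline and as follow-up values.

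The open wording adds a second problem: the adjusted hazard ratio can depend on covariates chosen after the data are seen, in an open-label trial. The model also matters to the authors' argument, because Limitations relies on the multivariable analysis to answer the inclusion of prevalent patients.

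Finally, the model is stated for death but sits under the composite primary endpoint, so the reader cannot tell which result the covariates govern.

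**Working it through.** **1. The plan's own figure.** Inputs from Sample size calculation: composite rates of 40% and 32% at 3 years, and "To reach statistical significance with α < 0.05 and 1-β > 80%, the sample size required is 1128". The abstract gives 1:1 allocation. Sidedness is not stated; I take two-sided.

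n per arm = [1.960 √(2 × 0.36 × 0.64) + 0.8416 √(0.40 × 0.60 + 0.32 × 0.68)]² / 0.08²
= (1.3305 + 0.5693)² / 0.0064 = 563.9, so 564 per arm and 1128 in total.

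This reproduces the stated number. It uses no covariates, so changing the covariate list does not alter it.

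**2. Planned effect as a hazard ratio.** Assuming exponential survival, HR = ln(0.68) / ln(0.60) = 0.755, and ln HR = −0.281.

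**3. Events.** 0.36 × 1128 ≈ 406, assuming 1128 patients followed for 3 years.

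**4. Illustration of attenuation.** If a share m of the log hazard ratio acts through covariates measured after randomisation, the adjusted hazard ratio is about 0.755^(1−m). Power (Schoenfeld) = Φ(|ln HR| × √(406/4) − 1.96).

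| Assumed share m | Adjusted HR | Power |
|---|---|---|
| 0 | 0.755 | 81% |
| 10% | 0.776 | 72% |
| 25% | 0.810 | 57% |
| 50% | 0.869 | 29% |

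The documents give no value for m. These rows are assumptions that show a range.

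**5. Check by simulation.** 1128 patients, 300 runs, 3 years of follow-up. Assumptions: one covariate with hazard ratio 1.36 per SD, baseline-to-follow-up correlation 0.7, and m = 25%.

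| Model | Mean HR | Power |
|---|---|---|
| Unadjusted | 0.764 | 80% |
| Adjusted for baseline value | 0.761 | 82% |
| Adjusted for follow-up value | 0.815 | 53% |

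With m = 0, all three models gave HR 0.755 to 0.759 and power 80% to 81%. The loss therefore comes from the mediated share and not from adjustment as such. Adding the baseline value gained about 1 to 2 points across the two settings. That is no larger than the simulation error of a single power figure, √(0.80 × 0.20 / 300) ≈ 2.3 points, although all models were fitted to the same simulated data.

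**The case against.** The strongest reply is that a baseline reading is natural. The firmly listed covariates are enrolment characteristics, Table 1 collects comorbidity once, hypertension can be read as a diagnosis present at entry, and hsCRP has a baseline value. This stands as far as it goes: a reader might infer that the plan adjusts for follow-up values, and the text does not say so. But it does not rule it out, and the ambiguity falls on the covariates where it can do harm.

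Second, the figures above use the composite, while the model is stated for death. That is correct. The documents plan no effect size for death, so no equivalent calculation can be made from them. A reader might also infer that the primary test is compromised. That is not established, because the composite comparison names no covariates.

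Third, such detail belongs in an analysis plan, which is not shown. That disposes of any complaint about missing site stratification or a missing interaction test. It does not dispose of the covariate wording, which the protocol chose itself and which an analysis plan would have to correct.

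Three further inferences are tempting and unsupported:

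- **Inter-dialysis weight gain as a target of BCM guidance.** Dry Weight Adjustment Strategy addresses it by educating all participants, in both arms. It needs the baseline restriction only because it can also be measured after randomisation.
- **Omitting baseline overhydration as an error that discards the key covariate.** The open list does not exclude it, leaving a baseline covariate out does not bias a randomised comparison, and the simulated gain is small.
- **The 41% versus 30% mortality in the cited observational study as a cap on the achievable benefit.** Those are deaths over an average of 3.5 years in 269 patients, not a 3-year composite. The protocol also allows dry weight to move in either direction, so correcting overhydration is not the only route to benefit.

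**Conclusion.** The point holds as a defect of specification. The list is open, no covariate is fixed at baseline, two named examples concern quantities that the protocol expects treatment to change, and the model's outcome does not match the endpoint it sits under. Whether this does harm depends on follow-up values being used. If they were, and 10% to 50% of the log hazard ratio acted through them, power would fall from about 81% to between 72% and 29%. Those figures rest on an assumed mediated share, exponential survival, about 406 events and the composite effect; they are not a forecast. The stated sample size of 1128 is unaffected. Adding baseline overhydration is a modest improvement to the model, not the repair of an error.

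**What to change.** In the Primary endpoint section:

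1. Close the list by replacing the open-ended phrase with named covariates.
2. State that every covariate, including hypertension, hsCRP and inter-dialysis weight gain, is the value recorded before randomisation.
3. Add baseline BCM overhydration. It is already collected in both arms and is prognostic in the plan's own source (41% versus 30% death), but expect only a small gain in precision.
4. State that the model serves the primary composite, and describe a model for death as a separate analysis if one is wanted.

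Stratifying the model by site and pre-specifying one interaction between treatment and baseline overhydration are optional. The interaction would have limited power.

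The cost is wording in the protocol or analysis plan. These baseline data fall within the collection already planned, and the sample size does not change. If the analysis plan already fixes these points, the two documents need only be made to agree.
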